### Interim analysis

There will be a formal interim analysis with the possibility of stopping early for futility (no prospect of a clinically meaningful treatment effect), at the point of 50% mature primary outcome data. Full details of the stopping boundaries and analysis will be detailed in a Statistical Analysis Plan (SAP), which the independent Data Monitoring Committee (iDMC) will approve prior to seeing unblinded data. The unblinded statistician will have no other role in the study while it is ongoing. The stopping rules are statistically non-binding. The iDMC may recommend early stopping of the study if the boundaries are crossed. They would make a recommendation to the independent Trial Steering Committee (TSC) who may or may not endorse that recommendation. The trial may stop at any time for safety if there is an excess of events in the intervention groups that is considered to generate avoidable harm. This decision would not be based on any statistical criterion and would be taken by the iDMC, then endorsed by the TSC.

### Recruitment and randomisation

Adults scheduled to undergo SET will be pre-screened by a member of the direct care team and invited to discuss the trial with a member of the research team. Informed consent will be obtained from each participant prior to participation in the trial, following adequate explanation of the aims, methods, anticipated benefits and potential hazards of the trial. The individual obtaining consent will be a registered healthcare professional and will have been delegated this duty by the principal investigator (PI) on the delegation log. Participants may provide their consent to participate in the trial electronically or in written form. Participants will initial alongside each statement on the consent form to confirm agreement with each clause. A copy of the consent form will be provided to the participant for their records. There is no defined time frame between initial consent and the baseline visit, however, confirmation that the participant’s consent is still valid prior to randomisation will be required in the baseline case report form (CRF).

Participants (n=6660) will undergo 1:1:1 web-based randomisation to one of three thromboprophylaxis strategies prior to undergoing SET. Randomisation will be conducted by an automated system linked to the Research Electronic Data Capture (REDCap) database setup via the Study Data Centre at the Edinburgh Clinical Trials Unit (ECTU), University of Edinburgh (a fully registered UKCRC Clinical Trials Unit, registration number 15). Participants will be assigned a study identification number by REDCap in sequential numerical order. Recruitment will commence on 1 January 2024 for 27 months. The study will close on 31 December 2026.

### Blinding

Clinicians and participants will be aware of their treatment allocation. Assessors, being those who perform the venous duplex ultrasound scan and those responsible for collecting follow-up data at 7- and 90 days post-procedure, will be blinded to the treatment allocation.

### Follow-up periods

Participants will undergo a lower limb venous duplex ultrasound scan at 21–28 days post-intervention to identify asymptomatic DVT. This is timed to capture the peak onset of events which is at 3 weeks.^29^ Participants will be further followed up remotely by telephone, online or short message service at 7 and 90 days with an expected VTE capture >95%.^29^ Longer term follow-up may be considered with award from a subsequent project grant to assess long-term efficacy of the intervention, hence contact at a later point will be included in the consenting process.

### Data collection and confidentiality

Participant data will be entered into the REDCap database by the local research teams. Source data stored at study centres will be archived locally as per local study operating procedures. Data and all appropriate documentation will be stored for a minimum of 10 years after the completion of the study, including the follow-up period. Details of procedures for CRF completion will be provided in a separate study manual. A formal data management plan will be constructed to describe the procedures involved in the data management activities and processes for the study so that it is managed and maintained in accordance with the Good Clinical Practice (GCP) guidelines, local Research and Governance Integrity Team (RGIT) standard operating procedures, appropriate regulatory requirements and the study protocol.

### Internal pilot

There will be an internal pilot to assess feasibility of recruitment over 9 months of recruitment to the trial, in which we will start recruiting from the (minimum) 40 centres. Site setup will be staggered over 9 months, that is, five centres per month. The target number of participants by the end of the 9-month internal pilot is 1450 participants. For the internal pilot, we will use stop–go criteria based on a Green–Amber–Red statistical approach (table 1).

**Table 1 T1:** Internal pilot of feasibility assessment at 9 months

Progression criteria	Red	Amber	Green
% Threshold	<10.9%	10.9–20.9%	>21%
Trial recruitment (of eligible participants)	<15%	15–17.6%	>17.6%
Recruitment rate/site/month	<5	5–7.1	>7.2
Number of centres opened	<25	25–40	>40
Total number of participants recruited	<725	725–1449	>1450

### Cost-effectiveness analysis

Two health economic analyses will be conducted, and a separate Health Economics Analysis Plan (HEAP) will be developed by the health economist detailing the proposed analyses. The main analyses will be performed from the perspective of the NHS and Personal Social Services, with secondary analyses from a societal perspective.

A within-trial analysis will compare the two pharmacological thromboprophylaxis strategies to compression alone over the 90 days of the study. Resource use items associated with treatments in primary and secondary care will be collected using case notes and self-completed patient diaries and costed using manufacturer list prices, previous literature and national reference costs. Days off work and normal activities and other patient-related costs will be collected for a secondary analysis. EQ-5D will be collected at baseline and follow-up, analysed using the NICE-approved tariff.

If the trial indicates that pharmacological thromboprophylaxis could be an effective therapy, a Markov (state-transition) decision model will be constructed to compare the cost-effectiveness of the two pharmacological thromboprophylaxis strategies and compression alone over a longer time horizon. The time horizon of the model will be 2 years, allowing extrapolation of sequelae of VTE events (such as PTS) over the longer term to quantify the impact of VTE on patient health via quality-adjusted life years (QALYs) and resource use. A preliminary model has been constructed based on published literature to identify the key variables that would need to be collected during the clinical study and to estimate the number needed to treat (NNT) to avoid one VTE, above which pharmacological thromboprophylaxis would not be considered cost-effective at NICE thresholds. This model conservatively assumes 30% of patients with VTE develop PTS, with 3% of those having severe PTS.

The minimum cost of purchasing 10 days of thromboprophylaxis and providing allocated time for administration training equates to ~£63.13.^30 31^ Our model assumes cost of treatment of VTE, non-severe and severe PTS as £451, £872 and £1547, respectively, and estimates of the respective utility decrement associated with symptomatic VTE and PTS are 0.8628, 0.7745 and 0.6752, respectively.^32^ Different durations of thromboprophylaxis will be modelled. These estimates will be reviewed at the time of the cost-effectiveness analysis, and any changes to these estimates will be updated.

Using a 2-year time horizon, incremental cost-effectiveness ratio of pharmacological thromboprophylaxis in comparison to no pharmacological therapy would be £13 339 per QALY if the NNT were 59 participants (1/0.017). For pharmacological thromboprophylaxis to be cost-effective at an NICE willingness to pay threshold of £20 000 per QALY, the NNT would need to be below 80.

Main analyses will be undertaken from perspective of the NHS and Personal Social Services, with secondary analyses from a societal perspective. Health economic analysis will be conducted according to NICE reference case and Consolidated Health Economic Evaluation Reporting Standards (CHEERS) guidelines, including sensitivity analyses and probabilistic sensitivity analyses.^33 34^ Results will be presented as estimates of mean incremental costs, effects and incremental cost per QALY.

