Despite its efficacy, SET is associated with thrombotic complications, presenting occurrences of venous thromboembolism (VTE) and endothermal heat-induced thrombosis (EHIT) at rates as high as 3.4%. VTE, encompassing deep vein thrombosis (DVT) and pulmonary embolism (PE), is a significant cause of disability and subsequent societal economic consequences.^15^ Hospital-acquired thrombosis (HAT), which is defined as the development of VTE within 90 days of a hospital episode, significantly contributes to morbidity and mortality, with statistics indicating a rate of 57 deaths per 100 000 admissions within the NHS.^16^ Complications following a DVT are substantial, with up to 50% of patients developing post-thrombotic syndrome (PTS), characterised by chronic leg pain, oedema and skin changes.^17 18^ Additionally, PE is associated with lifelong functional and psychological repercussions, ultimately posing a risk of death during the index event.^19 20^ EHIT, encompassing any thrombus forming within 4 weeks of endovenous ablation and extending from the treated vein towards or into a deep vein, is categorised into four classes. EHIT classes 3–4 involve significant thrombus extension into and encompassing the deep vein, often necessitating treatment similar to that for DVT.^9 10^ SET presents a unique VTE risk compared with other short-stay surgical procedures, exhibiting a VTE rate comparable to that observed in major joint surgeries.^16^ Comparable day-case surgical procedures such as inguinal hernia repair or laparoscopic cholecystectomy exhibit a notably lower VTE rate of 0.3%.^21^

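### The decision model stops at 2 years although the protocol calls the sequelae chronic or lifelong; report a longer horizon beside it and label the ICER and the NNT limit of 80 as 2-year figures

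*Protocol article*

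**What the plan says.** All of this is in the protocol article.

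- **Horizon of the planned model** (Cost-effectiveness analysis): "The time horizon of the model will be 2 years, allowing extrapolation of sequelae of VTE events (such as PTS) over the longer term". The model is built only if the trial indicates that prophylaxis could be effective.
- **Horizon of the published figures** (same section): the £13,339 per QALY at an NNT of 59 is introduced with "Using a 2-year time horizon, incremental cost-effectiveness ratio of pharmacological thromboprophylaxis". The limit follows from the same model: at a "willingness to pay threshold of £20 000 per QALY, the NNT would need to be below 80". The section describes the NNT limit as the point beyond which prophylaxis would not count as cost-effective.
- **Nature of the sequelae** (Introduction): PTS, in up to 50% of patients after a DVT, is described by chronic pain, swelling and skin changes. For PE, "PE is associated with lifelong functional and psychological repercussions, ultimately posing a risk of death during the index event".
- **Inputs** (Cost-effectiveness analysis): "The minimum cost of purchasing 10 days of thromboprophylaxis and providing allocated time for administration training equates to ~£63.13"; "cost of treatment of VTE, non-severe and severe PTS as £451, £872 and £1547, respectively"; 30% of VTE cases develop PTS, 3% of those severe; utility values 0.8628, 0.7745 and 0.6752.
- **Room to revise**: the cost and utility estimates will be reviewed, sensitivity and probabilistic analyses are planned, and a separate Health Economics Analysis Plan (HEAP) will follow. No horizon other than 2 years is named.

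**The concern.** Costs and benefits fall at different times. Prophylaxis is paid for at the start, while the benefit of an avoided VTE accrues for as long as its sequelae would have lasted. A 2-year model therefore carries the full cost and only part of the benefit. The protocol gives no reason for stopping there, and its own description of the sequelae points to a longer period.

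Cost-effectiveness is one of the stated aims. An effect that is real and statistically significant, but smaller than the design target, could fall on the wrong side of £20,000 per QALY only because of where the model ends.

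**Working it through.** **Inputs.** From Cost-effectiveness analysis: drug cost £63.13; VTE £451; PTS £872 (non-severe) and £1547 (severe); PTS probability 0.30, severe share 0.03; utility values as listed. Assumed, because the article does not give them: baseline utility 1.0, PTS cost and loss recurring yearly, and the durations below. The article labels the utility values as decrements, but its ICER is matched only if they are read as utilities; read literally they give roughly £1,200 to £4,400 per QALY.

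**Per-year PTS quantities, per VTE avoided.**
- QALY loss: 0.30 × [0.97 × (1 − 0.7745) + 0.03 × (1 − 0.6752)] = 0.0685
- Cost: 0.30 × (0.97 × 872 + 0.03 × 1547) = £268

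**Step 1: reproduce the 2-year figures.**
- C = 451 + 2 × 267.7 = £986
- Q = (1 − 0.8628) + 0.0685 = 0.2057
- ICER = (59 × 63.13 − 986) / 0.2057 = £13,309 (stated £13,339)
- NNT limit = (20,000 × 0.2057 + 986) / 63.13 = 80.8 (stated 80)

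Half a year of VTE loss plus two years of PTS loss gives the same Q: 0.5 × 0.1372 + 2 × 0.0685 = 0.2057. The durations actually used cannot be recovered, but both readings stop at 2 years.

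**Step 2: extend to 5 years, all else fixed.** Years 3, 4 and 5 each add 0.0685 QALY and £268, multiplied by the share still affected and discounted at an assumed 3.5%. With yearly resolution rate r from year 3:

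f = (1 − r)/1.035² + (1 − r)²/1.035³ + (1 − r)³/1.035⁴

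Then Q = 0.2057 + 0.0685f, C = 986 + 268f, and the limit is (20,000Q + C)/63.13.

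| r | f | Q | C | NNT limit, 5 years | ICER at NNT 59 |
|---|---|---|---|---|---|
| 0 | 2.707 | 0.391 | £1,711 | 151 | £5,147 |
| 10% | 2.206 | 0.357 | £1,577 | 138 | £6,017 |
| 30% | 1.394 | 0.301 | £1,360 | 117 | £7,849 |
| 50% | 0.801 | 0.261 | £1,201 | 102 | £9,683 |

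**Step 3: which results are exposed?** NNT 80 is an absolute reduction of 1/80 = 1.25%. Take 1998 analysed per group (2220 less 10%), a control rate of 2.7% and two-sided alpha of 2.5% (critical z = 2.24, ignoring the interim look). A reduction of 1.05% gives a pooled rate of 0.02175, a standard error of √(2 × 0.02175 × 0.97825/1998) = 0.00462 and z = 2.28. Observed reductions of about 1.05% to 1.25% (NNT about 95 down to 80) could therefore be significant and still miss the 2-year limit. All of that band lies inside the 5-year limit of 102, even with half of PTS cases resolving each year.

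**Step 4: sensitivity to another unstated input.** With baseline utility 0.9 instead of 1.0, the 2-year limit is about 40 to 46 under the two duration readings, and the 5-year limit without resolution is about 84 to 90.

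**The case against.** The best defence is that NNT 80 is not a decision rule. It comes from a preliminary model built to identify key variables. The final analysis will report incremental costs, effects and cost per QALY with sensitivity analyses under the NICE reference case, and the HEAP may add horizons. This stands as far as the number 80 goes. It does not remove the point, because the same 2 years is fixed for the planned Markov model and the promise to review covers only the cost and utility estimates.

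A reader might infer more than the documents support:

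- **That 80 is too strict and prophylaxis would be wrongly rejected.** This is a net claim, and only the horizon was varied. The £63.13 is a minimum cost, no bleeding cost or loss is listed, and the match implies a baseline utility of 1.0. The VTE utility is for symptomatic events, whereas the primary outcome also counts asymptomatic DVT. All of these push the other way.
- **That most of the avoided harm falls after year 2.** The Introduction gives no duration or persistence for PTS. With 30% resolving yearly, the limit levels off at about 133 even over 40 years, so only (133 − 81)/133 = 39% of it accrues after year 2. Limits near 200 need slow or no resolution.
- **That only one year of PTS is counted.** Step 1 shows that two years fits equally well.
- **That lifelong PE harm strengthens the case for prophylaxis.** The pooled PE rates under Sample size and study duration are 0.216% with prophylaxis and 0.058% with compression alone. The authors warn of confounding by indication, but these figures do not clearly favour prophylaxis, and the calculation above contains no PE state.

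Finally, the trial observes 90 days and lists no PTS outcome, so any longer horizon rests on outside data. That is a reason to show both horizons, but not to omit the longer one.

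**Conclusion.** The point holds in a limited form and is a cheap improvement. The 2-year horizon sits badly with the protocol's own account of chronic and lifelong sequelae. With the other inputs fixed, it biases the ICER against prophylaxis. Moving to 5 years raises the NNT limit from about 80 to between about 102 and 151, for yearly PTS resolution from 50% down to none. This rests on 3.5% discounting, continuing PTS costs, baseline utility 1.0 and no mortality, none of which the article states.

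The design target of NNT 59 passes at either horizon. The conclusion could change for effects with NNT just above 80, in particular the significant band of about 80 to 95. The documents do not show whether 80 is too low or too high once all inputs are corrected.

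**What to change.** - In Cost-effectiveness analysis and in the HEAP, run the Markov model over a horizon long enough for chronic sequelae: lifetime, discounted, with PE outcomes and an explicit PTS resolution rate varied in scenario analysis. Report it alongside the 2-year result.
- Where the ICER and the NNT limit are given, label £13,339 and NNT below 80 as 2-year figures from the preliminary model, and give the longer-horizon equivalents as a range.

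The cost is wording and extra model cycles, with no new patients or trial data. The downside is heavier reliance on external extrapolation. PTS persistence is partly a structural assumption, so it needs structural scenario analyses as well as the planned probabilistic sensitivity analysis.

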### Data monitoring, safety and quality control

An independent TSC and iDMC have been convened. The role of the TSC is to provide overall supervision of trial conduct and progress and ensure the study adheres to GCP principles. The role of the iDMC is to oversee the safety of the trial participants, and the iDMC will be the only oversight committee that sees unblinded data as the trial progresses, which they will keep in strict confidence. Details of membership, responsibilities and frequency of meetings for the TSC and iDMC have been defined in separate charters.

The Trial Management Group will oversee trial progress. All adverse events (AEs) will be collected and recorded on the REDCap database. Causality and relatedness will be assigned by the local PI or other appropriately trained and delegated individual. Research sites will inform the coordinating centre of all serious adverse events (SAEs) within 24 hours of knowledge of the event.

A study-specific risk assessment has been prepared in preparation for the study by the trial manager and study sponsor, which will be updated as required during the course of the trial. The frequency, type and intensity of monitoring visits will be detailed in a separate Data Monitoring Plan (DMP). The DMP will also detail the procedures for completion and sign-off of monitoring reports. In the event of a request for a trial site inspection by any regulatory authority, the study coordinating team must be notified as soon as possible. Participating investigators must agree to allow trial-related monitoring, including audits, Research Ethics Committee (REC) review and regulatory inspections, by providing access to source data and other trial-related documentation as required. Participant consent for this must be obtained as part of the informed consent process for the trial. The trial coordinating centre will centrally review eCRF data for errors and missing key data points on an ongoing basis.

Quality control will be performed according to Imperial College internal procedures. The study may be audited by a quality assurance representative of the sponsor. All necessary data and documents will be made available for inspection. The study may be subject to inspection and audit by regulatory bodies to ensure adherence to GCP and the UK Policy Framework for Health and Social Care Research.

### Patient and public involvement

Regular sustained patient and public involvement (PPI) has been undertaken to design and guide the study. Successful focus groups and interviews were held with patient representatives longitudinally throughout the trial development to gain insights into patients’ lived experiences and gather feedback on potential trial designs. Online surveys were also conducted with the wider venous community to inform the plain English summary. The patient-facing documentation has been designed in collaboration with three patient representatives. Two patient advisers have agreed to sit on the TSC, as well as review updated patient-facing documentation and assist with the dissemination of study results. An online survey of key stakeholders was also undertaken at the UK’s largest national conference to ascertain acceptability among clinicians of the proposed trial design.

## Ethics and dissemination

The Study Coordination Centre has obtained approval from the London Brent REC (23/LO/0261). Protocol amendments will be submitted to the sponsor for review before applying for approval from the REC, Health Research Authority (HRA) and Medicines and Healthcare Products Regulatory Agency (MHRA) and updating the ICRCTN record accordingly. The study must also receive confirmation of capacity and capability from each participating NHS Trust before any research activity is carried out. The study will be conducted in accordance with the recommendations for physicians involved in research on human subjects adopted by the 18th World Medical Assembly, Helsinki 1964 and later revisions. Study findings will guide international clinical practice and stimulate key updates to international guidelines. Results will be published in high-impact journals alongside presentation at national and international vascular and haematology societies.
